### Intervention procedure

The 8 sessions of the intervention occur weekly for about 90 min per session. Each session focuses on a particular theme including Introduction and Defining Stigma, Common Myths and Facts about HIV Transmission, Common Myths and Facts about Prevention of Mother-To-Child Transmission (PMTCT), The Road to Self-Acceptance and Freedom: Coping Strategies, Coping with Discrimination: Social Support and Self-Disclosure, The Road to Self-Acceptance and Freedom Part 2: Automatic Thoughts, What Matters Most, Review, and Graduation. Homework is assigned at each session and reviewed the next session. Certificates are issued to participants who complete the intervention (≥ 5 sessions) in a graduation ceremony. In consultation with local experts, we developed a concluding ceremony intended to convey “WMM” (i.e. “good mother” status) via the bestowing of ceremonial shawls that are typically provided when women become married and are ready to bear children. Finally, participants can leave this study at any time and, if choosing to withdraw, may decide to inform the study staff as to why, but are not required to do so.

### Training process

Following initial manual development, Steering Committee members convened in Botswana and trained a local clinical expert (SR), prospective psychology graduates trained in counseling, and peer co-leaders (i.e., women who had been identified with HIV during their own pregnancies) over an intensive 3-day period. The training included using the manual and stigma intervention skills in order to prepare the clinical and peer co-leaders to implement the intervention. To further refine the manual, co-leaders suggested modifications after each session, and extensive adaptations were made to further reflect cultural norms and concerns that were key to psychoeducation for HIV and stigma. After training, we expected ≥ 2 peers to agree to co-lead intervention groups. Preference was given to those who showed capacities to challenge stigma and who were willing to co-lead an intervention after individual stigma training. We envisioned a hierarchy developing in terms of capacity building in that the local clinical expert would then train a new cohort of peer co-leaders, with the clinical psychologist committee member (VJ) observing this process. The goal was to establish a “train the trainer” model in which there will be a cohort of local trainers on the MME manual to sustain this work and continue to reach women.

### Intervention fidelity

During the development phase of the MME manual, the Steering Committee included a licensed clinical psychologist consultant (VJ) who is a stigma and culture expert and specializes in cognitive behavioral therapy (CBT). This consultant was also on site during the co-leader training and interfaced directly with the peers, acting as the central evaluator for this pragmatic clinical trial. Her role also included developing the fidelity checklist for the MME manual. She monitors fidelity through weekly supervision calls with the local clinical expert and co-leaders, in which she provides a clinical lens to ensure the tenets of CBT are being met, confirm adherence to the MME manual per respective weekly sessions, and assess co-leader burnout. In regard to co-leader assessment, she additionally inquires about length of intervention sessions, quantity of sessions per week, and how peers are processing difficult information covered during the sessions.

### Comparator: treatment as usual

Control participants receive TAU, including using free ART and antenatal services as they wish. Budget constraints do not allow us to implement a time and attention placebo control condition; this threat to validity in this pilot study will be accounted for in a future RCT. Control condition participants are assessed on all primary outcomes at the same time points as the intervention group (Fig. 2), except for immediately following intervention.

### Dissemination policy

We will submit manuscripts to peer-reviewed journals with the Botswana team as lead and senior authors. We will also submit an NIH R01 proposing a multisite RCT of our stigma reduction intervention assuming success of this pilot study. In addition, we will communicate findings to participants as well as community and local stakeholders. At the end of the observation period, we will request consent from the participants to permit us to contact them using the contact information they have shared in order to invite them to a meeting where results will be communicated and feedback gathered. For the communities and local stakeholders, we have received support from the Botswana National Aids Coordination Agency (NACA) and we have invited them to participate throughout the study, including the design, intervention training, and results dissemination workshop. Once the study has been analyzed and findings are ready for sharing, we will approach them and the Botswana PEPFAR Coordination unit for opportunities to present the findings to key stakeholders (e.g. PEPFAR Implementing Partners). Finally, our team will also be submitting abstracts for both USA-based and international conferences to further share our findings.

Topics suggested for presentation or publication will first be presented to the Principal Investigator (LHY). Per suggested topic, explanation and justification for proposed authors will be submitted and reviewed by the full research team. Once a topic is approved, a writing committee will be established and the person who leads the presentation or publication may be considered as the lead author, but will need to confirm any final versions with the full team prior to submission. The Principal Investigator will be the lead author for the main outcomes study. All study staff who contribute intellectual elements to study design, study administration, data analysis, and manuscript development will be named as an author on all forthcoming publications.

The protocol team will make a de-identified data set publicly available a year after study completion in order to allow sufficient time for preliminary analyses and publications to be initiated by the study team. Contact with the Principal Investigator (LHY) will enable access to the dataset when available as well as data collection materials inclusive of informed consent forms.

### Assessments and outcome measures

All assessments are enumerated in Table 1, including their domain (name of the outcome), specific measurement, metric, method of aggregation, and time points. The three main time points are (1) baseline (< 28 weeks gestational age), post-intervention (immediately following completion of 8-session intervention, intervention group only), and follow-up (16 weeks postpartum). Primary outcomes for the mother include HIV stigma, psychosocial outcomes, treatment adherence, and HIV outcomes (e.g., viral load). Secondary outcomes for the infant include birth outcomes and early infant health. Stigma and psychosocial outcomes are collected via self-report questionnaires; all other outcomes are collected via health/medical records for the mother and infant. In addition, there are no additional studies using participants’ data and there are also no biological specimens that will be collected. If there are other studies to be conducted, there will be a separate procedure for additional consent.

**Table 1 Tab1:** Overview of measures

Assessment measure	Baseline (< 28 weeks gestational age)	Post-MME	Follow-up (16 weeks postpartum)	Comparison metric

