**Methods:**

This study will test MME against treatment as usual (TAU) among pregnant mothers diagnosed with HIV and their infants. Outcomes will be assessed during pregnancy and 16 weeks postpartum. Women who meet eligibility criteria are assigned to MME or TAU. Women assigned to MME are grouped with others with similar estimated delivery dates, completing up to eight intervention group sessions scheduled before week 36 of their pregnancies. Primary outcomes among mothers include (i) reducing self-stigma, which is hypothesized to mediate improvements in (ii) psychological outcomes (quality of life, depression and social functioning), and (iii) adherence to antenatal care and ART. We will also examine a set of follow-up infant birth outcomes (APGAR score, preterm delivery, mortality (at < 16 weeks), birth weight, vaccination record, and HIV status).

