**Covariates**				
Demographic measures	ALL	MME	ALL	N/A
Alcohol use (AUDIT)	ALL	MME	ALL	N/A
Sexual behavior (5 items)	ALL	MME	ALL	N/A
Intimate partner violence (WAST)	ALL	MME	ALL	N/A
**Qualitative** (open-ended; differs at each time points)	MME	MME	MME	N/A
**HIV metrics:** CD4 count and viral load (IDCC records/electronic medical record system)			ALL	1
**Birth outcomes:** birth weight, gestational age, APGAR scores (Delivery Summary Sheet)			ALL	1
**Infant health:** infant mortality, infant HIV status, feeding method, vaccinations, hospitalizations (dates, diagnosis) (“Under 5 Card”: asked from mother at 4 month follow-up)			ALL	1

1 Bivariate comparison of mean (median) scores at 16-week follow-up between intervention and control group

2 Bivariate comparison of change in mean (median) scores from baseline to 16-week follow-up between intervention and control groups

3 Bivariate comparison of mean (median) scores at baseline and post-MME within intervention group

4 Bivariate comparison of mean (median) scores at baseline and 16-week follow-up within intervention group

5 Bivariate comparison of mean (median) scores at post-MME and 16-week follow-up within intervention group

*ALL* all participants

*MME* only intervention participants

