#### Stigma

Stigma is measured by two validated scales and three additional items. The Berger HIV Stigma Scale is an established 40-item scale to measure stigma among PLWHA that has good reliability (alpha = 0.96) and validity [86]. The WMM HIV Cultural Stigma Scale in Botswana (HCSS-B) is a new 20-item scale developed specifically to measure culturally salient and protective aspects of stigma for HIV-positive women in Botswana, which has demonstrated good reliability for each of two subscales (alpha = 0.90 each) and validity [87]. Three specific study-developed items gauge how stigma interacts with Botho, a Setswana concept related to the qualities of being a good person (e.g., Botho phrase—“A person is a person because of other people”—*motho ke motho ka batho*).

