We will then build exploratory linear (continuous outcomes) or logistic (dichotomous outcomes) regression models to examine the effect of study arm on primary and secondary outcomes, and examine mediating effects of stigma on primary outcomes in mothers and exploratory outcomes in infants. We will prioritize objective measures in examining antenatal and ART outcomes and use self-report measures as a check on these findings. We will examine changes in predictors (e.g., stigma) between time points by creating difference variables and also examine these predictors as time-varying covariates in the regression model using generalized estimating equations (GEE) and structural equation models (SEM). A focus will be to examine whether changes in primary outcomes in mothers from baseline to post-intervention predict changes in primary outcomes at follow-up. If possible, SEM will also be used to examine structural relationships between latent constructs in the conceptual framework (e.g., among stigma subscales) and measured variables. Statistical significance will be assessed as *p* < 0.05. Statistical analysis will be conducted in Stata 16.

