### Sample size and power

Power calculations were done using Power Analysis and Sample Size Software (PASS 2019) [99]. Given the exploratory and pragmatic nature of the study, we calculated power based on the Wilcoxon rank-sum (Mann-Whitney *U*) test for primary outcomes (measured continuously) based on an intent-to-treat analysis. We assume a 3:1 rate of intervention to control participants. Example group sample sizes of 5 (control) and 15 (intervention) achieve > 85% power to detect a median difference of 1.0 using a two-sided Mann-Whitney *U* or Wilcoxon rank-sum test assuming that the actual data distribution is normal when the significance level (alpha) of the test is 0.05 [100–104]. An example sample size of 40 achieves > 80% power to detect a Spearman rank correlation of >|0.45| using a two-sided hypothesis test with a significance level of 0.05. These results are based on 5000 Monte Carlo samples from the bivariate normal distribution under the alternative hypothesis [105, 106]. We will also calculate power post hoc based on the data collected in this study (actual sample size and effect size) before we begin analysis.

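### Twelve maternal measures are labelled primary, ten with two unranked between-arm comparisons, all at p<0.05, and the lists of primary outcomes disagree

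*Protocol article*

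**What the plan says.** The Assessments and outcome measures section of the protocol article names four maternal domains: "Primary outcomes for the mother include HIV stigma, psychosocial outcomes, treatment adherence, and HIV outcomes (e.g., viral load". The subsections that follow under Primary outcomes fill them.

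- **Stigma:** "Stigma is measured by two validated scales and three additional items". These are the Berger scale, the HCSS-B and the Botho items.
- **Psychosocial:** five measures (PROMIS-8, CES-D, abridged PCL-5, WHODAS-12, social support).
- **Adherence:** antenatal care and ART.
- **HIV metrics:** CD4 count and viral load, with the method of analysis to be settled after the records are collected.

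Table 1 gives each of the first ten measures all five comparison metrics, of which two are between arms. Metric 1 is "Bivariate comparison of mean (median) scores at 16-week follow-up between intervention and control group". Metric 2 compares the change from baseline to the same visit. CD4 count and viral load have metric 1 only.

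The Statistical analysis section sets one threshold for all of this: "Statistical significance will be assessed as *p* < 0.05".

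The primary lists differ by place. The abstract gives "psychological outcomes (quality of life, depression and social functioning" plus self-stigma and adherence, with no HIV outcome. The Primary outcomes section words CD4 count and viral load as an expected consequence of the three listed domains. The Statistical analysis section leaves them out of the primary outcomes.

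**The concern.** The plan names self-stigma as the first primary outcome but does not say which of three measures represents it, or whether the 16-week level or the change from baseline decides. Nothing else ranks the 12 measures. An analyst who follows the plan exactly can therefore report as a primary finding any measure, on either comparison, that falls below 0.05. The error rate of that reporting rule is not 5%. A reader also cannot tell whether viral load, the most objective of the maternal measures, is a primary outcome. What is at stake is how a reader should weigh a single significant primary result when the next trial is being planned.

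**Working it through.** The plan states no overall false-positive rate, so it offers no figure of its own to reproduce. The steps below derive one.

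**1. Measures.** 3 stigma + 5 psychosocial + 2 adherence + 2 HIV metrics = 12.

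**2. Between-arm tests (Table 1).** 10 measures × 2 comparisons + 2 HIV metrics × 1 = 22. Taking only the 16-week level gives 12. Without the HIV metrics the counts are 10 and 20.

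**3. Threshold.** 0.05 per test (Statistical analysis). Two-sided, as in Sample size and power: "using a two-sided Mann-Whitney *U* or Wilcoxon rank-sum test".

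**4. Independent tests.** The chance of at least one p<0.05 when no measure differs between arms is 1 − 0.95^k.

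- k = 10: 1 − 0.599 = 40.1%
- k = 12: 1 − 0.540 = 46.0%
- k = 20: 1 − 0.358 = 64.2%
- k = 22: 1 − 0.324 = 67.6%

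**5. Correlated tests.** Outcomes reported by the same women will be correlated. The documents give no correlations, so a common correlation ρ between measures is assumed and varied. Two-sided z-tests were simulated (400,000 runs for 12 tests, 200,000 for 22).

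The level and the change on one measure share the same follow-up value, so they cannot be independent. If the baseline–follow-up correlation is r, with equal variances, the level and the change correlate at √((1 − r)/2): 0.59 at r = 0.3, 0.50 at r = 0.5 and 0.39 at r = 0.7. The 22-test column builds this in; its ranges run over r = 0.3 to 0.7.

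| ρ between measures | 12 tests (level only) | 22 tests (level and change) |
|---|---|---|
| 0 | 46.0% | 64–66% |
| 0.3 | 39.7% | 57–59% |
| 0.5 | 31.9% | 47–50% |
| 0.7 | 23.3% | 36–38% |

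**6. Influences left out.** With the example sizes of 5 and 15, the exact rank-sum test rejects in about 4.3% of null samples, not 5%. For 12 independent tests that gives 1 − 0.957^12 = 41%, slightly lower. Testing the two HCSS-B subscales separately, or both sources of antenatal visit counts, would raise the figures.

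**7. The lists side by side.**

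| Place | Psychosocial outcomes | CD4 count and viral load |
|---|---|---|
| Abstract, Methods | three named | not mentioned |
| Assessments and outcome measures | domain only | primary |
| Primary outcomes, opening paragraph | examples only | worded as a consequence |
| Psychosocial outcomes; HIV metrics | five named | under the Primary outcomes heading, analysis left open |
| Statistical analysis | domain only | not among the primary outcomes |

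**The case against.** The strongest reply is that this is a small, non-randomised pilot, described as exploratory in Sample size and power and meant to inform a later randomised trial. Multiplicity adjustment is often left to an analysis plan, which is not shown. Both points stand. They lower the weight of the finding, and the missing adjustment alone is no finding. They do not remove it. The Statistical analysis section labels only the pre/post analyses and the regression models exploratory, not the between-arm comparison of primary outcomes. A later document also cannot reconcile primary lists that already disagree here.

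A reader might infer more than the documents support.

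- **A 68% error rate.** 67.6% treats level and change on one measure as independent. With that link modelled, the ceiling is 64–66%. There is no firm lower limit either, because it depends on the assumed correlation.
- **An error rate of this size for stigma alone.** The figures pool all four domains. Stigma has 3 level tests, at most 1 − 0.95^3 = 14% under independence, or 6 tests with change, at most 1 − 0.95^6 = 26%.
- **Another 30 uncontrolled within-arm tests.** The Statistical analysis section already calls the pre/post work exploratory, so these are not counted here.
- **A conflict between the opening of Primary outcomes and the Psychosocial outcomes subsection.** The former gives examples only, so the two are compatible.
- **Success defined as any significant test.** The Dissemination policy makes the next grant application conditional, "assuming success of this pilot study", but ties success to no p-value or outcome.

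There is also some ranking within adherence: objective measures take priority over self-report. It does not extend to the other domains.

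**Conclusion.** The concern holds as stated in the heading. Twelve maternal measures are called primary, ten carry two between-arm comparisons with neither put first, self-stigma is not linked to one score, and the status of CD4 count and viral load differs between sections. The chance of at least one false-positive primary result is about 23–46% for 12 tests and about 36–66% for 22, at least four times the nominal 5% throughout. Dropping the HIV metrics does not rescue it: under independence, 10 tests give 40% and 20 tests at most 64%.

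The counts and the conflicting lists are read directly from the document. The percentages rest on assumed correlations of 0 to 0.7 between measures, equal variances at the two visits, a true null on every measure and tests close to their nominal size. Bias from non-random assignment is a separate matter and is not in these figures. For a pilot this should be corrected, but it does not invalidate the study.

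**What to change.** Before analysis:

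1. Name one stigma score at 16 weeks as the primary outcome. Which scale best represents self-stigma, the Berger scale or the one developed for this setting, is for the investigators to choose and justify.
2. Name one between-arm comparison as primary. One option is the follow-up score adjusted for its baseline value, which fits the adjustment for baseline differences promised in the Discussion. Keep the change-score comparison as a sensitivity analysis: allocation is not random, so the two can disagree and both should be seen.
3. Make the other maternal measures secondary. Report them as estimates with 95% confidence intervals and no significance claims, or with Holm adjustment.
4. Align the abstract, Assessments and outcome measures, Primary outcomes and Statistical analysis on which psychosocial outcomes count and whether CD4 count and viral load are primary.

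No data collection changes. The cost is wording in the protocol, and in any analysis plan or registry entry that repeats it, and fewer results that can be called significant.

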**Stigma outcomes**				
Berger HIV Stigma Scale	ALL	MME	ALL	1,2,3,4,5
WMM HIV Cultural Stigma Scale in Botswana (HCSS-B)	ALL	MME	ALL	1,2,3,4,5
Botho (3 items)	ALL	MME	ALL	1,2,3,4,5
**Psychosocial outcomes**				
Quality of life (PROMIS-8)	ALL	MME	ALL	1,2,3,4,5
Depressive symptoms (CES-D)	ALL	MME	ALL	1,2,3,4,5
Post-traumatic stress symptoms (PCL-5)	ALL	MME	ALL	1,2,3,4,5
Social functioning (WHODAS-12)	ALL	MME	ALL	1,2,3,4,5
Social support (6 items)	ALL	MME	ALL	1,2,3,4,5
**Treatment adherence**				
Antenatal adherence	ALL	MME	ALL	1,2,3,4,5
ART adherence (ACTG questionnaire)	ALL	MME	ALL	1,2,3,4,5
**Covariates**				
Demographic measures	ALL	MME	ALL	N/A
Alcohol use (AUDIT)	ALL	MME	ALL	N/A
Sexual behavior (5 items)	ALL	MME	ALL	N/A
Intimate partner violence (WAST)	ALL	MME	ALL	N/A
**Qualitative** (open-ended; differs at each time points)	MME	MME	MME	N/A
**HIV metrics:** CD4 count and viral load (IDCC records/electronic medical record system)			ALL	1
**Birth outcomes:** birth weight, gestational age, APGAR scores (Delivery Summary Sheet)			ALL	1
**Infant health:** infant mortality, infant HIV status, feeding method, vaccinations, hospitalizations (dates, diagnosis) (“Under 5 Card”: asked from mother at 4 month follow-up)			ALL	1

1 Bivariate comparison of mean (median) scores at 16-week follow-up between intervention and control group

2 Bivariate comparison of change in mean (median) scores from baseline to 16-week follow-up between intervention and control groups

3 Bivariate comparison of mean (median) scores at baseline and post-MME within intervention group

4 Bivariate comparison of mean (median) scores at baseline and 16-week follow-up within intervention group

5 Bivariate comparison of mean (median) scores at post-MME and 16-week follow-up within intervention group

*ALL* all participants

*MME* only intervention participants

### Primary outcomes

Primary outcomes among mothers include (i) reducing self-stigma, (ii) psychosocial outcomes (e.g., quality of life, social functioning), and (iii) treatment adherence (antenatal care, ART), which should result in improvements in HIV outcomes (CD4 count, viral load).

#### Stigma

Stigma is measured by two validated scales and three additional items. The Berger HIV Stigma Scale is an established 40-item scale to measure stigma among PLWHA that has good reliability (alpha = 0.96) and validity [86]. The WMM HIV Cultural Stigma Scale in Botswana (HCSS-B) is a new 20-item scale developed specifically to measure culturally salient and protective aspects of stigma for HIV-positive women in Botswana, which has demonstrated good reliability for each of two subscales (alpha = 0.90 each) and validity [87]. Three specific study-developed items gauge how stigma interacts with Botho, a Setswana concept related to the qualities of being a good person (e.g., Botho phrase—“A person is a person because of other people”—*motho ke motho ka batho*).

